**1. INTRODUCTION**

1.1 Scientific background

In malignant bile duct stenosis, a small percentage of patients with malignant bile duct stenosis fail to undergo endoscopic retrograde cholangiopancreaticography (ERCP). This is due to anatomical changes or a non-cannulated papilla. Percutaneous Transhepatic Cholangiodrainage (PTBD) has been the method of choice for years after unsuccessful ERCP and is widely available. However, numerous publications have reported a relatively high complication rate and 30-day mortality of up to 33% (1), making it necessary to establish a new reserve procedure for bile duct drainage. With endosonographically guided cholangiodrainage (EUCD), such a procedure has been established in recent years, since the initial description by Giovannini M in 2001 (2). In EUCD, the bile duct is punctured transmurally (through the stomach or intestinal wall) from inside the body. Four main drainage procedures are used: EUS-guided antegrade drainage via the papilla (EUS-AD), which is most similar to PTBD in principle, since it maintains the normal anatomy (bile flow via the papilla or jejunal loop in biliodigestive anastomosis), the most common EUS-guided hepaticogastrostomy (EUS-HGS), the EUS-guided choledochoduodenostomy (EUS-CDS) and the EUS-guided rendez vous procedure with ERCP (EUS-RV).

A recently published meta-analysis on percutaneous versus endosonographic bile duct drainage (3) concluded that the technical success rate of both procedures is equivalent, but that PTBD has a lower clinical success rate as well as more complications and a higher rate of re-interventions. It was therefore concluded that endosonographic bile duct drainage should be preferred to PTBD. However, the listed retrospective and prospective comparative studies either provide no information about the PTBD technique performed or use PTBD in the comparative arm in a way that does not correspond to the possibilities of this method.

The following is a commented overview of the comparative studies between PTBD and EUCD (12) (**Table 1**):

| **Author** | **Study type** | **PTBDs (n)** | **Adverse events (n)** | **Re-interventions (mean frequency)** | **Method of PTBD access** | **Special comments** |
| --- | --- | --- | --- | --- | --- | --- |
| Artifon 2012 (4) | Prospective | 12 | 3 (25%) | Not analyzed | fluoroscopic and ultrasound guidance | 4 external drainages before metal stent insertion |

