**2. OBJECTIVES AND ENDPOINTS**

Primary objective and primary endpoint

The primary objective of the study is to show that PTBD is not inferior to EUCD in terms of technical success rate. The technical success rate is defined as the successful implantation of a metal stent into the bile duct system (= successful drainage of the contrast medium via the metal stent within one minute after injection).

The primarily technical success of the intervention is decisive for the further procedure following the examination (reintervention necessary ? surgery necessary ?) and is presumably almost identical to the clinical success of the intervention, which can only be verified after 7 days (drop in bilirubin value ≥ 50%). The technical success rate was therefore preferred to the clinical success rate as the primary endpoint.

In PTBD there is only one possibility of metal stenosis insertion across the tumor stenosis in the common bile duct (blunt). In EUCD, the additional option of transluminal stent placement in the context of EUS-HGS or EUS-CDS remains.

The prompt (1 week) implantation of a metal stent after the application of an external drainage in PTBD is also considered a technical success. However, the application of an external drainage is counted as "reinvention".

Secondary objectives and secondary endpoints

In addition to the technical success rate, both interventions will be compared descriptively with regard to other endpoints. All endpoints or points in time refer to the technically successful intervention.

1. Clinical success rate of bile extraction, defined as reduction of the bilirubin value of ≥ 50% 7 days after technically successful intervention in relation to the baseline value before intervention.

2. The occurrence of at least one complication (including death) within 30 days (description + count)

3. Duration of bile duct intervention (PTBD/EUCD) in minutes

- for PTBD: from the application of the local anaesthetic to the application of the skin dressing

- for the EUCD: from the insertion of the endoscope to the removal of the endoscope

4. Post-interventional pain sensation on day 1 and day 7 after intervention (in relation to baseline before intervention): visual analogue scale

5. Length of hospital stay (from the day of the first intervention to the day of discharge) in days

6. Number of re-interventions between the first intervention and the end of the follow-up

(n) after 6 months.

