3.2 Duration and timetable

The duration of the clinical trial for the individual participant is 6 months follow-up time after intervention.

The total duration of the clinical trial is expected to be 36 months. The recruitment of patients will start on 1.12.2018.

Total duration:

Duration of the clinical phase: [36 months].

[30 months]

FSI (first subject in): [1.12.2018]

LSI (last subject in): [1.12.2020]

LSO (last subject out): [31.5.201]

DBL (database lock): [30.06.2020]

Completion of statistical analysis: [1.10.2020]

Final study report: [1.12.2021]

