4.4 Inclusion criteria

Patient is at the age of ≥ 18 years with inoperable, malignant underlying disease and shows a clinically relevant stenosis of the common bile duct (= subhilar). An ERCP was not successful or could not be performed due to surgically induced anatomical changes

Laboratory chemical, at least twofold increase in the total bilirubin value of: ≥ 2.0 mg/dl

The malignant underlying disease was histologically confirmed

An abdominal sonography was performed

A further sectional imaging of the abdomen is available in order to rule out, in addition to planning the intervention, an advanced underlying disease with a severely limited prognosis (e.g. metastatic liver):

CT abdomen or MRT abdomen

Written consent has been obtained

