5.6 Pre- and concomitant diseases

Pre- and concomitant diseases besides the underlying malignant disease that are present at the time of informed consent are not documented, as they are not expected to have a relevant impact on key endpoints of the study such as the technical and/or clinical success rate or the occurrence of complications of the intervention. By differentiating between Overall Survival and Disease Specific Survival, it is possible to specify the proportion of disease-specific causes (related to the underlying malignant disease causing the biliary obstruction) in the death of patients. It is expected that the underlying malignant disease is the main life-limiting factor in the observation period.

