Serious adverse events (SUE) since intervention (yes/no)

Control visit no.2 (7 days after technically successful intervention

Intensity of pain on the visual analogue scale (0-10) Date Bilirubin determination (after initial intervention)

Laboratory chemical result of the bilirubin determination (after initial intervention, in mg/dl)

Duration of hospital stay from day of intervention (inclusive) to day of discharge (date of hospital discharge, if later than 7 days, please add later!)

Re-intervention(s) since control visit 1 (yes/no) Complication(s) since control visit 1 (yes/no)

Serious adverse events (SUE) since intervention (yes/no)

Control visit no.3 (6 months after intervention) and/or study completion visit

The final study visit coincides with the follow-up visit after six months. To calculate the Overall Survival or Disease Specific Survival, it is noted whether the patient is still alive or when he/she died and why (date of death, calculation of survival time in days, cause of death). If the patient is not examined at the trial centre or has died in the meantime, it must be ensured that the relevant data on re-intervention, adverse events, date of death and cause of death can be obtained by calling the family doctor or relatives.

Data that are documented within the framework of the study:

Date of end of study/last contact

Reason for termination:

- Regular termination of the study (yes/no)

- Patient has died (yes/no)

Date of death

Cause of death on the ground of the underlying malignant disease (yes/no)

Cause of death other than underlying malignant disease (yes/no)

Cause of death unclear (yes/no)

Revocation of consent (yes/no)

Patient no longer appeared/follow-up data no longer to be collected (yes/no)

Intervention not successful, no new attempt

Other (specification)

Chemotherapy carried out during the course (yes/no)

Chemotherapy protocol (name): first line/second line/third line (multiple answers possible)

- Gemcitabine mono (yes/no)

- Gemcitabine/Nab-paclitaxel (yes/no)

- FOLFIRINOX (yes/no)

- Cisplatin/Gemcitabine (yes/no)

- FLO (T) (yes/no)

- FOLFIRI (yes/no)

- Paclitaxel/Ramucirumab (yes/no)

- Ramucirumab mono (yes/no)

- 5 FU mono (yes/no)

- Other chemotherapy/immunotherapy (yes/no)

Other therapy (but no chemotherapy) performed (yes/no)

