The evaluation of further secondary endpoints is done in the ITT set. With regard to the complication rate, PTCD is expected to have a lower complication rate than EUCD. No missing values are implanted during the evaluation of secondary endpoints. The evaluation is purely descriptive. Appropriate statistical methods are used according to the underlying distribution. For continuous endpoints, the mean, standard deviation, median, interquartile distance, and minimum and maximum are reported separately and in total for the two groups. For categorical endpoints, absolute and relative frequencies are given, also separately for the two groups and in total. Event times are displayed and evaluated using survival time analysis methods (e.g. Kaplan Meier). Descriptive p-values are given together with 95% confidence intervals. In the EUCD group, descriptive p-values are also divided by method (see 5.1). In addition, unless defined in the secondary endpoints, adverse events are evaluated and compared.

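### Secondary endpoint 6 counts re-interventions up to 6 months without regard to time at risk, so unequal survival between the arms would distort the comparison of late re-interventions

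*Protocol*

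**What the plan says.** Section 2 lists secondary endpoint 6 as "Number of re-interventions between the first intervention and the end of the follow-up", with the window closing at 6 months. Section 3.2 sets the same horizon: "The duration of the clinical trial for the individual participant is 6 months follow-up time after intervention". No rule is given for a patient who dies or is lost before then.

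Section 5.5 puts two kinds of event into the count. The first is repeat procedures needed to get a metal stent in place. The second is procedures for closure, migration or malfunction of the stent in the months afterwards. Sections 2 and 5.1 add certain drainages around the first procedure.

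Section 9.2 evaluates the further secondary endpoints descriptively in the ITT set, without imputation and with descriptive p-values and 95% confidence intervals. On summaries it says: "For continuous endpoints, the mean, standard deviation, median, interquartile distance, and minimum and maximum are reported". Categorical endpoints get frequencies, and survival methods are named for event times only. The re-intervention count is assigned to none of these classes.

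Section 4.4 admits patients with "inoperable, malignant underlying disease", and section 5.6 says: "It is expected that the underlying malignant disease is the main life-limiting factor in the observation period". Section 5.3 states that allocation is by centre, not by randomisation.

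**The concern.** A patient who dies in week 3 has had almost no time for a stent to block or migrate. In a plain count that patient contributes zero, the same as a patient who lives six months with a working stent. If one arm loses patients earlier, its count of late re-interventions falls for a reason unrelated to how well the drainage works.

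Because each centre contributes to one arm only, equal survival cannot be presumed. Section 5.6 also says that concomitant diseases are not documented, which limits later adjustment. The protocol allows for unequal follow-up elsewhere: sections 7.2.3 and 7.2.4 censor survival at last contact. Endpoint 6 has no counterpart.

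The result is meant to be used. Section 1.2 wants re-intervention rates determined so that a preferred method can be named, and section 1.3 asks how far the higher re-intervention rate attributed to PTBD really applies.

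**Working it through.** **Inputs from the protocol.** Follow-up is 6 months (sections 2 and 3.2). Late stent failures are expected (5.5), as are deaths from the malignancy during follow-up (5.6). Section 1.1 cites 30-day mortality of up to 33% from the PTBD literature, which is not a 6-month survival figure for either arm. The protocol states no figure for endpoint 6 that could be reproduced. Its sample size (section 9.1) rests on technical success and is not affected.

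**Inputs assumed.** Survival is exponential with median m months. The late re-intervention rate is constant while alive and the same in both arms. None of these values is in the protocol, so a range is shown.

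**Step 1: time at risk.** With λ = ln 2 / m, the mean months alive within the window are (1 − exp(−6λ)) / λ.

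| Median survival | λ per month | Dead by 6 months | Mean months at risk |
|---|---|---|---|
| 3 | 0.231 | 75% | 3.25 |
| 4 | 0.173 | 65% | 3.73 |
| 5 | 0.139 | 56% | 4.07 |
| 6 | 0.116 | 50% | 4.33 |

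**Step 2: apparent effect when the true monthly rates are equal.** The ratio of expected counts is the ratio of mean months at risk, whatever the common rate.

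- 4 v 5 months: 3.731 / 4.074 = 0.92, about 8% fewer.
- 4 v 6 months: 3.731 / 4.328 = 0.86, about 14% fewer.
- 3 v 6 months: 3.246 / 4.328 = 0.75, 25% fewer.
- Equal survival: 1.00, no distortion.

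At an assumed 0.15 per month, 3 v 6 months gives 0.15 × 3.246 = 0.49 against 0.15 × 4.328 = 0.65 late re-interventions per patient. Conversely, a true rate 1 / 0.75 = 1.33 times higher in the shorter-lived arm would be fully hidden.

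**Step 3: dilution by early events.** Let f be the share of the longer-lived arm's re-interventions that occur in the first days, with equal early risk in both arms. The count ratio becomes f + (1 − f) × r, where r is the ratio from step 2. For r = 0.75 and f = 0.5 it is 0.5 + 0.5 × 0.75 = 0.875, or 12.5% fewer. For f = 1 it is 1.00.

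**Step 4: would a single rate over all events cure it?** Dividing by time at risk gives (f + (1 − f) × r) / r. For r = 0.75 this is 1.00 at f = 0, 0.875 / 0.75 = 1.17 at f = 0.5, and 1.33 at f = 1. When events are front-loaded, one overall rate makes the shorter-lived arm look worse than it is. Restricted to late events, the ratio is 1.00 under the assumed constant rate.

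**Step 5: would cumulative incidence with death as a competing event cure it?** With late rate κ = 0.15, the 6-month incidence is κ / (κ + λ) × (1 − exp(−6(κ + λ))).

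- Median 3: 0.15 / 0.381 × (1 − exp(−2.286)) = 0.394 × 0.898 = 0.35.
- Median 6: 0.15 / 0.266 × (1 − exp(−1.593)) = 0.565 × 0.797 = 0.45.

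The incidence is still lower in the shorter-lived arm although the rates are equal.

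**The case against.** **The analysis may be left to the SAP.** Section 9 defers detail to an SAP that is not shown, and section 9.2 promises methods suited to the underlying distribution. An offset could still be added there. This stands in part. The endpoint itself, however, is fixed in the protocol as a count over a nominal window, and a clause about distribution does not address exposure.

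**The summary is not fixed as a mean.** A reader might infer that the plan commits to mean, SD and median for this endpoint. It does not: those are prescribed for continuous endpoints, and the count is not named. The point rests on the absence of any link to time at risk, not on a particular summary.

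**The link with survival is partly recognised.** Section 5.4 says the effect of chemotherapy on re-intervention and survival is taken into account, and section 5.3 says the same of patient characteristics. Overall survival is reported too, so an imbalance would be visible. This softens the point, but neither section mentions follow-up time.

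**The endpoint is descriptive.** This stands. Only complications follow the primary test in the hierarchy.

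**The count has its own use.** This stands. The literature table in section 1.1 gives mean re-interventions per patient, and a count describes the burden patients actually bear. It should not be dropped.

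**Early events are common and a rate can overcorrect.** This stands, as steps 3 and 4 show, and it shapes the fix.

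**Conclusion.** The point holds in conditional form. As defined, endpoint 6 understates late re-interventions in whichever arm has shorter survival. At equal true monthly rates the shortfall is about 8% for median survival of 4 v 5 months and 25% for 3 v 6 months. It is zero if survival is equal, and smaller in proportion to the share of early events. These figures rest on exponential survival, a constant late rate and assumed medians.

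Two stronger readings are not supported. One is that the count will favour a particular arm: the documents do not say that survival will differ, or in which direction. The other is that a known large share of patients will die within 6 months. Inoperable malignancy and the expectation in section 5.6 make deaths likely, but no 6-month figure is given, and section 4.4 uses imaging to rule out a severely limited prognosis.

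The change is worth making because it is cheap and serves a stated aim. It does not touch the primary analysis.

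**What to change.** - Keep the per-patient count to 6 months.
- Report re-interventions needed to complete stent placement separately from those after technical success. Decide in advance where a drain left at the stenting session belongs; it does not depend on survival, so it fits the first group.
- For re-interventions after technical success, add a rate per patient-month alive and under follow-up, from a Poisson or negative binomial model with log follow-up time as offset. Start the clock at the technically successful intervention.
- Show these results beside overall survival by arm.
- Cumulative incidence of first re-intervention, with death as a competing event, may be added as a description of burden if re-intervention dates are recorded. State that it does not remove the effect of unequal survival.

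The follow-up time is already available: section 6.3 records the intervention date, and section 6.4 records date of death and "Date of end of study/last contact". Two data items need checking against the CRF. Section 6.3 lists the number of PTBDs before stenting but no matching EUCD item. At control visit 2, section 6.4 lists re-interventions as yes/no only, so number and timing relative to technical success should be captured.

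The cost is protocol or SAP wording and a little extra analysis of a descriptive endpoint. Sample size is unchanged.

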**3. STUDY CONCEPTION/ DESIGN**

3.1 Study design

Prospective, multicentre, non-randomized, open, confirmatory, 2-arm non-inferiority study in parallel group design

3.2 Duration and timetable

The duration of the clinical trial for the individual participant is 6 months follow-up time after intervention.

The total duration of the clinical trial is expected to be 36 months. The recruitment of patients will start on 1.12.2018.

Total duration:

Duration of the clinical phase: [36 months].

[30 months]

FSI (first subject in): [1.12.2018]

LSI (last subject in): [1.12.2020]

LSO (last subject out): [31.5.201]

DBL (database lock): [30.06.2020]

Completion of statistical analysis: [1.10.2020]

Final study report: [1.12.2021]

**4. PATIENT AND CENTRE SELECTION**

4.1 Number of patients

According to the case number calculation (Chapter 9.1), 212 patients, i.e. 106 patients per intervention group, are needed to achieve a power of 80% under the assumptions made. Since this is a non-randomised study, in which only one intervention is offered within a centre, recruitment should not be terminated until at least 106 patients have been enrolled in both arms. If the centres belonging to the same intervention arm have together reached the recruitment target of 106 patients, but the centres of the other arm have not yet reached it, recruitment may continue.

The recruitment and treatment of patients will be carried out in the respective study centres. Each centre participating in the study should be able to enrol at least 10 patients within the planned recruitment period of 24 months.

If the total number of cases is not reached by the planned recruitment end (31.01.2020), the recruitment period may be extended if necessary. If recruitment is accelerated, recruitment will be terminated earlier accordingly.

4.2 Trial centres

The present study is conducted multicentre (5 centres PTBD, 5 centres EUCD).

Due to the complexity of the interventions, only one of the two interventions is carried out in each centre, namely the one that is also carried out there by default.

When selecting the centres for the study, care is taken to ensure that the same number of centres participate for both intervention groups.

4.3 General criteria for patient selection

No patient may be enrolled in the clinical trial more than once.

4.4 Inclusion criteria

Patient is at the age of ≥ 18 years with inoperable, malignant underlying disease and shows a clinically relevant stenosis of the common bile duct (= subhilar). An ERCP was not successful or could not be performed due to surgically induced anatomical changes

Laboratory chemical, at least twofold increase in the total bilirubin value of: ≥ 2.0 mg/dl

The malignant underlying disease was histologically confirmed

An abdominal sonography was performed

A further sectional imaging of the abdomen is available in order to rule out, in addition to planning the intervention, an advanced underlying disease with a severely limited prognosis (e.g. metastatic liver):

CT abdomen or MRT abdomen

Written consent has been obtained

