4.5 Exclusion criteria

Individuals who meet one of the following criteria will not be enrolled in the clinical trial:

There is limited blood clotting (Quick < 50%, PTT > 50 sec., platelet count > 50/nl)

There is an extrahepatic bile duct carcinoma of the Klatskin type in stage bismuth 2-4 or an intrahepatic bile duct carcinoma

The malignant underlying disease is operable or can be cured by chemotherapy (e.g. aggressive non-Hodgkin's lymphoma)

The patient is pregnant or breastfeeding

The patient participates in another interventional study on EUCD or PTBD

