6.1 Screening visit

A paper-bound explanation of the study (own form) for the intervention (commercial form) and the sedation or anaesthesia (commercial form) of the patient is provided. Each potential study patient will receive a CT or MRI abdomen in addition to an abdominal sonography. The inclusion and exclusion criteria are checked (Case Report Form , p.2). Every patient who has been positively screened is included in the study if written consent is obtained (Case Report Form, p. 1). In the case of patients who are still capable of giving birth, a possible pregnancy is excluded by pregnancy tests.

It is assumed that almost all positively "screened" patients want to undergo an intervention under study conditions. In this situation, surgery is usually either not possible (pre-operated abdomen, advanced tumour disease) or is associated with a considerable risk. The performance of a PTBD/EUCD is therefore mostly without alternative. The screening list lists (separate form) which patients have been screened positively (inclusion and exclusion criteria fulfilled). Should a patient not be included in the study (e.g. because of refusal to participate in the study), this is briefly explained.

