6.2 Baseline visit

Facts of the clinical picture are documented (Case Report Form,p.3) . Cause of malignant bile duct obstruction, date of first diagnosis of the malignant underlying disease, cause of unsuccessful or for anatomical reasons not feasible ERCP.

The bilirubin value in mg/dl as an expression of the bile duct obstruction or cholestasis is measured and noted. The baseline visit should be performed the day before the intervention. Depending on the timing within the centre, baseline visit can be on the same day as screening visit if the intervention is scheduled for the following day.

Data that are documented as part of the study:

Demographics

- Gender

- Age

- Size

- Weight

Cause of the malignant bile duct obstruction (no multiple answers)

- Pancreatic carcinoma

- Distal bile duct carcinoma or extrahepatic bile duct carcinoma (Bismuth I)

- Gall bladder carcinoma

- Stomach cancer

- Duodenal carcinoma

- Papillary carcinoma

- Metastasis of another malign disease

- Other cause

Date of first diagnosis of the underlying malignant disease

Cause of unsuccessful or for anatomical reasons not feasible ERCP (no multiple answers)

- Gastric outlet stenosis/duodenal stenosis (tumour-related or benign cause)

- Difficult to probe the optic disc using ERCP

- For (partial) gastrectomy

- Biliodigestive anastomosis

- Following bariatric surgery

- Other cause

Laboratory chemical result of bilirubin determination (in g/dl) Pain intensity on the visual analogue scale (0-10)

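### Poor-prognosis disease is to be ruled out by imaging but is neither defined nor recorded, so a prognosis imbalance between arms could not be seen or adjusted for

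*Protocol*

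**What the plan says.** Protocol 4.4 lists among the inclusion criteria: "A further sectional imaging of the abdomen is available in order to rule out, in addition to planning the intervention", followed by what is to be ruled out: "an advanced underlying disease with a severely limited prognosis (e.g. metastatic liver". It gives no life expectancy, stage or extent of liver involvement.

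Protocol 4.5 opens with "Individuals who meet one of the following criteria will not be enrolled in the clinical trial" and lists five items: impaired clotting, Klatskin tumour of Bismuth 2-4 or intrahepatic bile duct carcinoma, operable or curable disease, pregnancy or breastfeeding, and participation in another EUCD or PTBD study. None concerns prognosis, stage or liver metastases.

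On screening, 6.1 states "Each potential study patient will receive a CT or MRI abdomen in addition to an abdominal sonography" and has the criteria checked, but does not say which finding makes a patient ineligible. The screening list shows "which patients have been screened positively (inclusion and exclusion criteria fulfilled").

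The baseline items in 6.2 are demographics, one cause of obstruction, date of first diagnosis, one reason for ERCP failure, bilirubin and pain. The nearest entry to stage is the cause option "Metastasis of another malign disease".

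Sections 4.2 and 5.3 fix one technique per centre, with five centres per arm and no randomisation. Section 5.3 assumes comparable groups and says that differences in patient characteristics are taken into account. The regression models in 9.2 name intervention, BMI and bilirubin, with technical success as the outcome.

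**The concern.** Take a patient with pancreatic cancer and liver metastases. One centre could enrol: imaging is available and no exclusion applies. Another could decline, because metastatic liver is the example named in 4.4. Both readings are defensible.

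In a trial randomised within centres, such differences would affect who is studied but not the comparison. Here the centre determines the technique, so a stricter or looser reading in the centres of one arm would appear as a difference between PTBD and EUCD. With five centres per arm, nothing guarantees that the readings balance.

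The loss could not be repaired later. An analysis plan can choose covariates only from data that were collected. At stake are the endpoints that depend on prognosis: overall and disease-specific survival and, possibly, the 30-day complication endpoint, which 9.2 tests at two-sided 5% once non-inferiority is shown.

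**Working it through.** **1. Can the data show who had liver metastases?** The cause of obstruction in 6.2 allows one answer. The patient above is coded as pancreatic carcinoma, with or without liver metastases. The metastasis option describes what blocks the duct, not the spread of the disease; the lymph-node metastasis at the liver hilus mentioned in 5.3 is an example. Date of first diagnosis is not stage. Section 5.6 leaves concomitant diseases unrecorded, and the data lists for later visits in 6.3 and 6.4 add no stage item. Chemotherapy is recorded, but after the intervention. Patients turned away on prognosis do not appear in a list of positively screened patients. The visit figure is not available here, but the itemised lists contain no such field.

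**2. Which endpoints are exposed?**
- Technical success (primary): 5.3 expects no relevant influence of patient characteristics on success, and nothing in the protocol speaks against that for liver metastases.
- Survival: 5.6 expects the malignant disease to be the main life-limiting factor, so its extent matters directly. These analyses are descriptive (9.2).
- 30-day complications: section 2 defines "The occurrence of at least one complication (including death) within 30 days". Section 8.1 limits recording to potential complications of the procedure and uses death as a severity grade. If the endpoint counts all deaths within 30 days, prognosis enters directly. If it counts only fatal procedural complications, the link is much weaker.

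**3. How large could it be?** The protocol has no figure for this. Its sample size (100 per group, 106 after 5% drop-out, 9.1) rests on technical success and does not depend on this criterion.

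For illustration, let *a* and *b* be the shares with liver metastases in the two arms, and *r1* and *r0* the 30-day event rates with and without them. With no technique effect, the expected difference between arms is (a − b) × (r1 − r0). All rates and shares below are assumed; *r0* is 12% throughout.

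| a v b | r1 | Expected rates | Difference | Chance of p < 0.05 |
| --- | --- | --- | --- | --- |
| 40% v 10% | 30% | 19.2% v 13.8% | 5.4 points | about 18% |
| 40% v 10% | 20% | 15.2% v 12.8% | 2.4 points | about 8% |
| 20% v 10% | 30% | 15.6% v 13.8% | 1.8 points | about 7% |
| 20% v 10% | 20% | 13.6% v 12.8% | 0.8 points | about 5% |

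First row: 0.4 × 30% + 0.6 × 12% = 19.2%; 0.1 × 30% + 0.9 × 12% = 13.8%.

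The last column uses a pooled two-proportion z-test with 106 per arm. For the first row, the pooled rate is 0.165, the null standard error √(2 × 0.165 × 0.835 / 106) = 0.051 and the critical difference 1.96 × 0.051 = 0.100. The standard error under the expected rates is √((0.192 × 0.808 + 0.138 × 0.862) / 106) = 0.0509. The upper tail is Φ((0.054 − 0.100) / 0.0509) ≈ 0.18; the lower tail adds about 0.001. The nominal level is 5%.

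**The case against.** A reader might infer that the protocol contradicts itself by wanting to keep out the population it describes elsewhere. The text does not support this. Inoperable disease is not the same as a severely limited prognosis. The sentence "In this situation, surgery is usually either not possible (pre-operated abdomen, advanced tumour disease") only explains why surgery is rarely an option. The metastasis entry in 6.2 is a cause of obstruction. What stands is an undefined term with no counterpart in 4.5.

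A reader might also infer that any available scan satisfies the criterion, or that the arms do apply different cut-offs. The first is too literal: the wording shows an intent to exclude, and inclusion criteria bind as much as exclusion criteria. The second is a possibility, not something the protocol states. Different readings by centre may partly average out within an arm, and nothing suggests that they line up with technique.

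It can fairly be added that the complication endpoint is mainly procedural, that survival is only descriptive, and that confounding is a general limit of this design. All of this lowers the weight of the point. It does not answer the central part: the protocol names a prognostic feature as a reason for imaging and then does not record it. Covariate choice may be left to the analysis plan, but data collection cannot.

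**Conclusion.** The point holds as a gap in definition and, more importantly, in data collection. Any imbalance in liver metastases or stage between arms would be invisible and could not be adjusted for, so the statement in 5.3 cannot be kept for this characteristic.

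The exposure is mainly in overall and disease-specific survival. For the 30-day complication endpoint it is smaller and uncertain, and turns on whether all deaths count or only fatal procedural complications. The primary non-inferiority conclusion is probably little affected.

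The size of any bias is unknown. The range of 0.8 to 5.4 points rests wholly on assumed event rates and imbalances; the upper end needs a 30-point difference between arms in the share with liver metastases and an 18-point difference in event risk. It shows what could go unnoticed and is not an estimate.

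**What to change.** - Add liver metastases (yes/no) and metastatic stage to the 6.2 baseline data, read from the CT or MRI that is already mandatory.
- Report both by arm and by centre. This is where a difference in how centres read the criterion would show.
- Include liver metastases as a covariate in adjusted analyses of survival and of 30-day complications.
- Reconcile 4.4 and 4.5 so that one uniform eligibility rule applies at all centres. Its content is for the investigators to decide. If the rule leaves no enrolled patients with liver metastases, the covariate falls away.

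The cost is two CRF fields, one covariate and the amendment wording, with no new examination. At the 10-20% complication rate expected in 9.2, 212 patients give about 21 to 42 events (0.10 × 212 and 0.20 × 212), enough to carry one further covariate in a small model. Adjustment would not remove confounding by other unrecorded differences between centres.
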